#### Health economic measures

Health-related quality of life (HRQoL) outcome measures are detailed in table 2.

#### Resource use

Data will be collected on healthcare, education and social care resource use for both the CYP and parents/carers, using a purposely designed resource use collection tool. The questionnaire was developed by the study’s health economics team at Nottingham following discussions with the study’s patient and public involvement (PPI) team and representatives. This was an iterative process until all parties including the PPI team and representatives, the health economics team and the wider TMG were reassured the questionnaire was fit for purpose. It collects data on all aspects of healthcare interventions including medication, inpatient and outpatient hospital visits and primary and community care use as well as societal and education costs. It also includes sections specifically designed to quantify the effect of time off work for parents/carers (including friends and family) to quantify the wider social cost, that is, implications for productivity. In addition, it measures effects on time lost from education or training for the child/young person because of emotional difficulties. A similar approach to capturing resource use information was employed by members of the study team for a feasibility trial involving parents and carers of children with attention-deficit/hyperactivity disorder (ADHD).^25^

These data will be attributable to the emotional difficulties of the young person and be self-reported by the parent/carer with online supplemental information obtained from CYP aged 16 and 17. Administrative records of treatments/interventions offered by CAMHS during the trial period may be considered as a online supplemental source of data.

10.1136/bmjopen-2021-053043.supp7Supplementary data

#### Sociodemographic data

The following sociodemographic data will be collected primarily from the participant-reported questionnaires; age at randomisation, sex, gender, ethnicity, paid employment and derived from the postcode of the child’s primary residence, the index of Multiple Deprivation score.

#### Data collection

Data will be collected through participant reported questionnaires (parent/carer and CYP self-report aged 11+) and from clinical records. Participant reported outcomes will be collected at baseline and 6 and 12 months post-randomisation (online supplemental appendix 7). Questionnaires are intended to be completed online by participants in the first instance—to maximise rates of completion and retention there will be an option for telephone completion, should participants have difficulty accessing or completing the questionnaires online.

Outcomes collected from records will be reported for the 12-month period following randomisation.

### Data management and analysis

#### Data management

Arrangements for data handling are specified in the data management plan. Central and on-site monitoring will be carried out as required following a risk assessment and as documented in the monitoring plan. Monitoring activities will be carried out by the coordinating centre on behalf of the trial sponsor.

Data will be held on servers located within The University of Nottingham data centres. Security is both physical (secure limited access) and electronic (behind firewalls, access via user accounts). Personal data recorded on all documents will be regarded as strictly confidential and handled and stored in accordance with the Data Protection Act 2018.

#### Statistical analysis

The primary approach to between-group comparative analyses will be by modified intention to treat (ITT) (ie, including all participants who have been randomised and without imputation of missing outcome data).

The primary comparative analysis will employ a generalised linear mixed model to compare the proportions in each group with a clinician-made diagnosis decision within 12 months of randomisation, adjusted for minimisation variables. The comparison will be presented as both an absolute (risk difference) and relative (risk ratio) effect, along with 95% CIs.

Secondary outcomes will be analysed using appropriate mixed effect regression models dependent on data type and will adjust for factors used in the minimisation and baseline value of the outcome where measured. For outcomes measured at multiple time points, these will be analysed using a mixed model with a treatment by time interaction to obtain estimates of treatment effect at each follow-up time.

Appropriate interaction terms will be included in the primary regression analyses in order to conduct subgroup analyses according to sex and age of the CYP.

Statistical analysis will be conducted using Stata V.17.0 (or later).

#### Health economic analysis

In accordance with NICE guidance, primary analysis will take an NHS and personal social services perspective. Unit costs will be attached to participant reports of healthcare resource use or recorded treatments/interventions offered by CAMHS. The cost of the DAWBA itself will be distributed at the participant level across the intervention arm of the trial. Sensitivity analyses will take a wider perspective to capture the broader societal costs inclusive of out-of-pocket expenses and productivity losses. Indices of HRQoL for the EuroQol-5 Domains (EQ-5D), EuroQol-5D-Youth (EQ-5D-Y) and Child Health Utility instrument (CHU9D) will be derived using relevant population tariffs, and quality-adjusted life-years (QALY) estimated using area under the curve.

The economic evaluation will take an incremental approach between the two groups using an ITT population (irrespective of treatment received) and a 12-month time horizon. The outcome for the primary cost utility analysis will be the joint young person and parent/carer QALYs. The outcome for the secondary cost-effectiveness analysis will be confirmed diagnosis decisions. Outcomes will be paired with their respective direct-to-NHS costs, bootstrapped and scattered on the cost-effectiveness plane to characterise the uncertainty in incremental estimates. Using the net monetary benefit framework,^26^ cost-effectiveness acceptability curves will be constructed to show the non-parametric probability the intervention is a cost-effective option, compared with usual care, across a range of willingness to pay thresholds per QALY, and within the secondary analysis per confirmed diagnosis decision. While the receipt of any diagnosis of emotional difficulties in young people would likely lead to large divergences in lifecourse outcomes, the heterogeneity of conditions considered for diagnosis (online supplemental appendix 5) renders CUA modelling across the lifecourse infeasible. Secondary analysis is expected to be fully captured within the 12-month time horizon.

A full statistical analysis plan and health economics analysis plan will be developed and agreed prior to database lock and unblinding of the analysing statistician and health economist.

### Embedded qualitative study

During the internal pilot, semi-structured interviews are undertaken with a sample of participants who consented to be invited to participate in qualitative interviews. Researchers, clinicians, service managers and commissioners are identified by site leads. The proposed sample size is 25 participants (parent/carer and CYP aged 16–17), 25 staff and 15 service managers and commissioners. Interviews address: (1) the feasibility of recruitment; (2) the acceptability and usability of the interventions and procedure; (3) how the intervention is used and how this deployment could be refined for the main trial. Interviews are conducted by the qualitative researcher (KN) in person, or by phone or video call based on participant preferences and pandemic restrictions.

A process evaluation, conducted during the main trial phase, will aim to identify the barriers and facilitators to implementation of the intervention. Semi-structured interviews will be conducted with a further sample of participants and clinicians to explore the perceived functioning of the intervention, the organisation of the service and reflective experiences on outcomes.

Qualitative interview data will be recorded and encrypted on a password-protected Dictaphone and transferred securely to medical transcription company Dict8 for transcription. Transcriptions will be anonymised. Audio files will be destroyed after transcripts have been checked. Anonymised transcriptions will be analysed and stored on password protected computers and the secure University of Nottingham server.

#### Qualitative analysis

All qualitative interview data will be initially analysed by the qualitative researcher (KN) using interpretative thematic approaches to coding, and adopt the framework method,^27^ with input from the qualitative lead (LT), chief investigator ([name]) and PPI leads ([name]). NVivo V.12 will be used to manage the qualitative data.

### Patient and public involvement

Prior to submission, the proposal was informed by consultations with a person with lived parent/carer experience of CAMHS, including contribution to and review of the proposal, recruitment strategy, participant trial experience and consideration of burden of the intervention, and establishing a PPI workstream.

Following award, the PPI Co-Investigator team recruited two representatives naïve of the study design to provide independent review of the trial via their membership of the TSC. Both TSC members are persons with lived parent/carer experience of CAMHS.

During study set up, PPI Co-Investigator expertise was used to support researcher recruitment via the design and deployment of role plays within interviews.^28^ This was to gain insight into candidates’ capabilities when dealing with sensitive and challenging participant scenarios. Additionally, they contributed to design of researcher training materials, to support standardised approaches across trial sites. Iterative and creative design PPI activities were integral in the development of the STADIA trial logo and branding to ensure accessibility and acceptability to CYP and parents.

Since study commencement participatory design approaches have seen PPI co-design of the resource use questionnaire, qualitative interviews and the protocol for a Study Within A Trial to support participant engagement with follow-up. Additionally, collaborative working between the PPI and Qualitative workstreams has enabled examination of the qualitative themes using principles of the Framework Method^27^ for independent verification of those themes.

Two PPI advisory panels have been established, meeting on average every 3 months since month 9 of the study. ‘STADIA PPI Panel’ has eight adult members, with lived parent/carer experience of CAMHS. ‘STADIA Labs’ has six CYP members, aged 15–19 at inception, with lived experience of CAMHS. These groups have been involved in many traditional activities such as review of the Participant Information Sheet (PIS) and consent forms, consultation on language and content for participant reminder text messages. PPI coproduction activities are also seeing the development of age appropriate study newsletters and the design of STADIA information videos including decision making about video concept, audience, message, aesthetic and content. PPI group members are provided with supplementary training about PPI practices and involvement opportunities. Due to the COVID-19 pandemic, PPI meetings have had to move online and so the PPI team are investing in knowledge transfer and upskilling PPI representatives in different ways of working and collaborating online.

There are a range of planned flexible opportunities for participating in project feedback and dissemination activities including cofacilitating and presenting at the interactive dissemination workshop/consensus meeting, publication authorship as peer researcher and presenting at conferences to showcase the project findings.

## Ethics and dissemination

### Ethics

The study was reviewed and received favourable opinion from the South Birmingham Research Ethics Committee (Ref. 19/WM/0133) on 12 June 2019; subsequent amendments have been approved. The current, approved protocol is version 4.0 dated 3 February 2021.

### Safety

The trial intervention is conceptually similar to usual clinical practice (ie, CYP referred to CAMHS may be sent questionnaires about their difficulties), therefore, the risks of the trial are considered comparable. The DAWBA is widely used in research for data collection therefore, although used as an intervention in the STADIA trial, the risks may be regarded as similar to those of an observational/questionnaire study. Data to inform safety oversight will therefore be collected during routine follow-up, from existing outcome measures. There is no separate adverse event or serious adverse event reporting.

The number of participants meeting predefined safety outcomes will be reported on an ongoing basis to the TMG and TSC. Data will be presented by arms to the data monitoring committee (DMC).

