### Consent

Prior to consent, eligibility will be confirmed (box 1) during telephone contact with the local STADIA researcher, who will also provide written and verbal information about the trial, answer questions and support the electronic consent/assent process. Participants who are eligible and provide verbal consent to participation during the call will be provided with a personal link to the online electronic informed consent/assent form (table 1, online supplemental appendices 2 and 3, respectively), enabling them to provide written informed consent/assent.

10.1136/bmjopen-2021-053043.supp2Supplementary data

10.1136/bmjopen-2021-053043.supp3Supplementary data

Box 1Eligibility criteriaInclusion criteria for the children and young people (CYP)Aged 5–17 years.Referred to outpatient multidisciplinary specialist Child and Adolescent Mental Health Services (CAMHS).Presenting with emotional difficulties.If aged <16, has an eligible individual with parental responsibility (see parent/carer eligibility criteria below) willing and able to participate in the trial.If aged 16–17, has capacity to provide valid written informed consent.If aged 16–17 and participating without a parent/carer, able to complete the assessment tool in English.If aged 16–17 and participating without a parent/carer, access to internet and email or telephone.Exclusion criteria for the CYPEmergency or urgent referral to outpatient multidisciplinary specialist CAMHS (ie, requires an expedited assessment) according to local risk assessment procedures.Severe learning disability.Previously randomised in the STADIA trial.Inclusion criteria for the parent/carerIndividual with parental responsibility for the CYP referred to CAMHS; this will be the CYP’s mother or father, legally appointed guardian or a person with a residence order concerning the CYP.Adequate knowledge of the CYP to be able to complete the assessment tool (ie, known for at least 6 months).Has capacity to provide valid written informed consent.Access to internet and email or telephone.Able to complete the assessment tool in English.Exclusion criteria for the parent/carerLocal authority representatives designated to care for the CYP.

**Table 1 T1:** Consent and participation

Age of CYP referred to CAMHS	CYP aged <11	CYP aged 11–15		CYP aged 16–17	
Initial contact with	Parent/carer			Depends on contact details provided with the CAMHS referral*	

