Consent provided by	Parent/carer	Parent/carer	Parent/carer	CYP AND parent/carer (optional)	CYP
Assent provided by	None	CYP (optional)	None	None	None
Participant(s)	Parent/carer only	CYP and parent/carer dyad	Parent/carer only	CYP and parent/carer dyad	CYP only
Primary participant†	Parent/carer	Parent/carer	Parent/carer	CYP	CYP
Secondary participant	None	CYP	None	Parent/carer	None
DAWBA completed by	Parent/carer	Parent/carer AND CYP	Parent/carer	CYP AND parent/carer	CYP
Research questionnaires completed by	Parent/carer report on CYP Parent/carer self-report	Parent/carer report on CYP Parent/carer self-report CYP self-report	Parent/carer report on CYP Parent/carer self-report	CYP self-report Parent/carer report on CYP Parent/carer self-report	CYP self-report

For all CYP aged <16 the initial contact about the study will be with the parent/carer. The involvement of CYP aged 11–15 will be at the discretion of the parent/carer.

*For CYP aged 16–17 if the CYP’s contact details are provided on the CAMHS referral the first contact about the study will be with the CYP who can choose to nominate a parent/carer to participate in the trial alongside them or participate alone. If the parent/carer’s contact details only are available the first contact will be with the parent/carer and the parent/carer will be asked whether the CYP can also be contacted but may choose to refuse this. The parent/carer will not be able to participate in the STADIA trial without the involvement or consent of the CYP.

†The primary participant is the person who must provide consent as a minimum requirement in order for randomisation to take place. Assent (of CYP aged 11–15) and parental consent (for CYP aged 16 and 17) may also be sought but is not mandatory and therefore will not be required prior to randomisation.

CAMHS, Child and Adolescent Mental Health Services; CYP, children and young people; DAWBA, Development and Well-Being Assessment; STADIA, STAndardised DIagnostic Assessment for children and adolescents with emotional difficulties.

The participation and consent/assent requirements for the trial are shown in table 1.

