Anxiety symptoms in the CYP	Revised CYP’s Anxiety Depression Scale (RCADS)	RCADS^33^ is a 47-item questionnaire that measures the reported frequency of various symptoms of anxiety and low mood. Each item is rated on a 4-point scale (never=0, sometimes=1, often=2, always=3). An overall anxiety and low mood score is generated, with separate sub-scale scores for separation anxiety, social phobia, generalised anxiety, panic, obsessive–compulsive disorder and major depression. RCADS demonstrates good psychometric properties.^34^ Total anxiety and depression scores range from 0 to 141. We will record scores for each of the six sub-scales. For analysis metric, we will use the total anxiety score. RCADS collected at baseline, 6 and 12 months post-randomisation.
Comorbid oppositional defiant/conduct disorder symptoms in the CYP	Strengths and Difficulties Questionnaire (SDQ)	SDQ^35^: A 25-item emotional and behavioural screening questionnaire for CYP. Each item is rated on a 3-point scale (not true, somewhat true, certainly true). Values of 0, 1 or 2 are assigned to each response. SDQ comprises five subscales and an impact supplement. The impact supplement asks effect of difficulties on homelife, friendships, education and leisure activities. SDQ has demonstrated reasonable psychometric properties.^36–39^ Scores on the ‘conduct problems’ subscale will be used in the analysis of this outcome. Subscale scores range from 0 to 10. SDQ collected at baseline, 6 and 12 months post-randomisation.
Functional Impairment in the CYP	SDQ	Impact supplement scores will be used to determine functional impairment. Impact scores range from 0 to 10. Collected at baseline, 6 and 12 months postrandomisation.
Self-harm thoughts in the CYP	CYP self-report self-harm measure	CYP will be asked to report the frequency of thoughts of self-harm. Frequency of thoughts of self-harm are rated over the last 6 months in the following categories and scored accordingly: Not at all (0) Once or twice Three or more times Collected at baseline, 6 months and 12 months post-randomisation.
Self-harm behaviours in the CYP	CYP self-report self-harm measure	CYP will be asked to report frequency of instances of self-harm behaviour. Frequency of self-harm behaviour are rated over the last 6 months in the following categories and scored accordingly: Not at all (0) Once Two or more times Collected at baseline, 6 months and 12 months post-randomisation.

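### Safety data come only from existing outcome measures, and the only listed self-harm measures are child self-report, so self-harm as such goes unmeasured in under-11s and in parent-only 11–15s

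*Protocol article*

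**What the plan says.** The Safety section treats the risks as comparable to usual practice and to those of a questionnaire study. It concludes: "Data to inform safety oversight will therefore be collected during routine follow-up, from existing outcome measures". It then states: "There is no separate adverse event or serious adverse event reporting". On reporting it says: "The number of participants meeting predefined safety outcomes will be reported on an ongoing basis to the TMG and TSC", with data by arm going to the data monitoring committee (DMC). The article does not list those safety outcomes.

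Table 2 (Secondary outcomes) has two self-harm rows, both using a self-report measure at baseline, 6 and 12 months:
- Thoughts: "CYP will be asked to report the frequency of thoughts of self-harm".
- Behaviours: "CYP will be asked to report frequency of instances of self-harm behaviour".

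Eligibility (Box 1) is "Aged 5–17 years", but child self-report starts later. The Data collection section says: "Data will be collected through participant reported questionnaires (parent/carer and CYP self-report aged 11+) and from clinical records". Table 1 makes the parent or carer the sole participant for every child under 11 and in one of the two arrangements for ages 11–15. The text beneath it adds: "The involvement of CYP aged 11–15 will be at the discretion of the parent/carer".

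**The concern.** A safety system that draws on existing outcomes can see only what those outcomes measure, and only in those who supply them. Here the self-harm rows have one type of informant, who is absent by design from part of the enrolled population.

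This matters because the intervention may affect access to care. Participants are identified before the referral decision. An algorithm-derived report that is not clinically rated goes into the clinical record, and referral acceptance is a secondary outcome. If the report contributed to care being declined or delayed, one place the harm could appear is in self-harm, crisis presentation or death. A by-arm count of self-harm would exclude the youngest children and the parent-only participants, and a death cannot be recorded on a self-report form.

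Among those who can self-report, an arm comparison is also open to selection. Participants know their allocation, and questionnaire return follows randomisation. The Table 1 footnote does not require assent at ages 11–15 before randomisation, so a young person's participation may be settled after allocation is known.

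**Working it through.** **Step 1. Who can supply a self-harm report (Table 1 against Table 2)**

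| Participation arrangement | Child or young person questionnaire | Self-harm measured |
|---|---|---|
| Under 11, parent/carer only | None | No |
| 11–15, dyad | Yes | If returned |
| 11–15, parent/carer only | None | No |
| 16–17, dyad | Yes | If returned |
| 16–17, alone | Yes | If returned |

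**Step 2. Whether another listed outcome fills the gap**

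- Outcomes from records cover referral acceptance, discharge, re-referral, diagnosis, treatment and their timing. None is defined as self-harm, crisis or emergency contact, or death.
- Re-referral within 12 months comes from records and does not depend on age or informant, but the article states no urgency flag.
- The resource use questionnaire asks about inpatient and outpatient visits and is mostly parent-reported, so it reaches younger children. No self-harm item is stated, and it is lost when the questionnaire is not returned.
- Parent-reported symptom and impact scores may show deterioration but are not a self-harm measure.

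**Step 3. The denominator**

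The plan gives no coverage figure for self-harm. Its sample size supplies only the denominator, and it reproduces. For 45% against 55%, 90% power and two-sided 5%:

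- n = [1.960·√(2·0.5·0.5) + 1.282·√(0.45·0.55 + 0.55·0.45)]² / 0.10², which gives 524 per arm.
- With continuity correction: 544 per arm, as stated.
- With 10% non-collection: 544/0.9 = 604.4, so 605 per arm and 1210 in total, as stated.

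**Step 4. Share with no self-harm report at a follow-up**

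All four inputs below are assumptions, because the article gives none of them:

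- u, share under 11: 0.20 to 0.50
- o, share aged 16–17: 0.15
- p, parent-only share among ages 11–15: 0.10 to 0.50
- r, non-response among young people due a questionnaire: 0 to 0.40

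Observed share = [(1 − u − o)(1 − p) + o] × (1 − r)

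| u | p | r | Observed share | Unobserved of 1210 |
|---|---|---|---|---|
| 0.20 | 0.10 | 0 | 0.65×0.90 + 0.15 = 0.735 | 0.265×1210 = 321 (27%) |
| 0.30 | 0.30 | 0.20 | (0.55×0.70 + 0.15)×0.80 = 0.428 | 0.572×1210 = 692 (57%) |
| 0.50 | 0.50 | 0 | 0.35×0.50 + 0.15 = 0.325 | 0.675×1210 = 817 (68%) |
| 0.50 | 0.50 | 0.40 | 0.325×0.60 = 0.195 | 0.805×1210 = 974 (about 80%) |

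Rows one and three have full response, so they bound the structural gap alone: 27% to 68%. Adding non-response takes the upper end to about 80%.

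**The case against.** The strongest reply is that the safety outcomes are predefined but not listed here. They may appear in the full protocol or the DMC charter, and an article may leave such a list to those documents. That stands as far as it goes. A reader might infer that the DMC sees only self-report counts from responders aged 11 or over, but nothing in the article says so. What the unseen list cannot do, on the article's own terms, is go beyond existing outcome measures, because the Safety section fixes that source. None of the outcomes listed captures self-harm from a parent or from records.

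Second, other measures reach all ages. Re-referral from records bears directly on a wrongly declined referral, and hospital visits are asked of parents. This also stands: safety oversight is not blind to deterioration in younger children. The gap is in self-harm identified as such.

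Third, this is a reasoned design choice. The report is an adjunct, urgent and emergency referrals are excluded, and an ethics committee gave a favourable opinion. The case for light-touch safety reporting is fair, but it does not address who is left unmeasured. A reader might take the Introduction's mention of self-harm and suicide as naming safety endpoints. It is a background association and sets none.

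Fourth, age is a minimisation factor, so leaving out under-11s limits coverage without biasing the arm comparison. That is right. The bias concern applies only to optional participation and questionnaire return.

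**Conclusion.** The point holds as a gap in measurement. With safety data restricted to existing outcomes and self-harm measured only by child self-report, self-harm as such is unobserved by design in all children under 11 and in parent-only participants aged 11–15. It is also unobserved wherever the young person's questionnaire is not returned, with no listed records-based self-harm outcome as back-up.

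The structural part follows from Tables 1 and 2 and needs no assumption. Its size does: 27% to 68% of 1210 with full response, and up to about 80% with non-response, under the assumed ranges. A single coverage figure would be only one point among these possibilities, and the documents do not support choosing one.

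The documents also do not support a claim that serious consequences would mostly go undetected, given the indirect signals from re-referral and hospital visits. This is a worthwhile and inexpensive improvement to safety data collection. It does not affect the primary analysis or the sample size.

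**What to change.** Add to the existing 12-month record proforma, for every randomised child whatever the age or participation arrangement:

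- documented self-harm events;
- urgent or emergency mental health referral or admission;
- death.

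Report these by arm to the DMC, with all participants whose records were reviewed as the denominator and the number randomised alongside. Present the self-report self-harm measure as supplementary, with its actual denominator by arm and age group. Reconcile the Safety section with Tables 1 and 2 by stating which groups each safety measure covers.

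The cost is a few extra fields on a record review already planned, for which the sample size section allows up to 10% non-collection of the primary outcome. Participants who stop questionnaires may still consent to data from records, so these fields can reach many whom the self-report measure misses. Extraction takes slightly longer, and records capture only events known to services, so the new counts will understate self-harm that never reached a service.
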